### Inspiratory Muscle Training (IMT)

The inspiratory muscle training (IMT) will build on the information the patients have obtained during the IBA and biofeedback session described above. The IMT will focus on training endurance and coordination of the posterior cricoarytenoid (PCA) muscle, aiming to reduce fatigue of the abducting capacity of the larynx and to enhance coordination and create a sense of laryngeal control. When performing the IMT sessions, it is of utmost importance that a functional diaphragmatic breathing pattern has been established, and that this breathing pattern is maintained throughout all the IMT sessions. Once the patient has demonstrated that he/she is able to perform breathing according to these principles, the IMT session can start according to this flow chart.

#### IMT Teaching Session at the Hospital

The maximal inspiratory mouth pressure (PI_max_) will be established, according to the instructions provided by the manufacturer (*POWERbreathe, Southam, UK*) (32). The resistance of the training device is set to 20–60% of maximum PI_max_.A flexible laryngoscope is positioned with its tip in the epipharynx, ensuring a good view of the laryngeal entrance, and secured using a headset.The patient then enters into the IMT teaching session, performed with the laryngoscope in place, with the patient facing the monitor that shows the laryngeal movements while the patient is practicing the IMT.a) The training device is positioned correctly in the mouth of the patient.b) The patient exhales slowly from TLC to RV, using at least 5 s to reach RV, emphasizing a correct posture, relaxation of potential tensions in the thoracic, shoulder and neck region, and minimal movements of the head and shoulders.c) From the RV position, the patient then performs a “determined” inspiration of short duration up to TLC against the resistance of the training device. A correct breathing technique is strongly emphasized; i.e., diaphragmatic breathing with minimal movements of the head and shoulders.d) During subsequent repeated training sessions: If TLC appears difficult to reach, it may be a sign of fatigue or an inappropriate breathing pattern.The technique and the pressure settings are adjusted as needed, in order to ensure that the larynx is kept maximally open (abducted) during the inspiration.

#### IMT Performed at Home

1) The patients will perform IMT at home, as they were instructed during the teaching session at the hospital.2) They will perform 30 loaded breaths twice daily for 5 days per week for 6 weeks with the resistance set to 20–60% of maximum PI_max_.3) It will be emphasized that it is of utmost importance that the breathing technique explained during the teaching session always must be applied at all subsequent IMT training sessions; i.e., they must ensure diaphragmatic breathing with minimal movements of the head and the shoulders.4) The IMT device will contain a memory card, thus ensuring that treatment compliance is measured, and that data from all training sessions are stored for later inspection.

There will be a video meeting 1 and 3 weeks after the in-house training session, lasting maximum 30 min. The patients will be asked to demonstrate how they perform their breathing practices, and corrected when necessary.

The patients are advised to use the knowledge they gain about breathing techniques and the experience they gain from the IMT sessions, when they perform exercise at home. The aim is to help the patients to develop a strategy on how to control his/her larynx during exercise, and to be able to continue exercising without experiencing dramatic EILO incidents. They will be informed that the best approach is to start practicing while performing low to moderate intensity exercise, and then gradually increase the intensity as they become more confident. It will be emphasized that the new breathing technique they are about to adopt will need to be repeated until it becomes adopted as a part of their automated breathing pattern.

For all three non-invasive treatment groups, there will be a video meeting 1 and 3 weeks after the in-house training session, lasting maximum 30 min. The patients will be asked to demonstrate how they perform their breathing practices, and corrected when necessary.

## Phase 3—Surgical Intervention

Surgery is currently available at our institution, irrespective of this treatment protocol, for patients with EILO who continue to exhibit EILO symptoms and still demonstrate supraglottic collapse ≥2 during a CLE test despite non-invasive treatment, and who are highly motivated for further treatment (11). Careful selection of patients adhering to these strict criteria is emphasized in the daily routine clinical work. The inclusion criteria for surgical treatment in the present study (Phase 3) are the same as those applied in the daily routine clinical work. The only exception is that the nature of the non-invasive treatment algorithm is stricter, and surgery is not hampered by availability.

Surgical treatment for severe supraglottic EILO is currently performed according to a procedure originally used to treat severe laryngomalacia (14). We do not know if it is possible to use a less radical or less extensive approach and still obtain sufficient symptom relief. We know from unpublished channels, that some are using less extensive procedures as in-office procedures. However, there are no formal reports from studies using such techniques. A less extensive surgical procedure that efficiently relieves EILO symptoms would clearly be preferable to the current relatively resource-intensive technique.

Thus, the aim of this surgical phase of the protocol is to test effects from two surgical techniques to treat severe supraglottic EILO:

Supraglottoplasty—full procedure under general anesthesia.Supraglottoplasty—minimally invasive procedure under general anesthesia.A control group receiving no further treatment, against which both methods will be compared to assess effect.

### Supraglottoplasty—Full Procedure

The surgeon informs each patient about the objectives of the procedure and the irreversible change of the laryngeal anatomy caused by this operation. The patient should understand the balance between the prospects of improvement and the risk factors involved; i.e., post-operative aspiration, scarring, infection, and bleeding. The supraglottoplasty is performed under general anesthesia by suspension laryngoscopy with use of CO_2_ laser and microlaryngeal instruments. The patient is intubated with an armored laser-tube which is positioned in the posterior midline to protect this area from laser injury. The laryngoscope (Benjamin-Lindholm from Karl Storz) is positioned into the vallecula and the operation field is visualized through a surgical microscope. The CO_2_-laser (Digital Acublade Lumenis) is attached to the microscope through a micromanipulator, laser energy adjusted to 2–4 W and focused with micro spot during the procedure. Releasing incisions are made anteriorly in both aryepiglottic fold. The depth of the incisions are limited to the cranial border of the ventricular fold (Figure 4).

**Figure 4 F4:**
[figure not shown]
Supraglottoplasty, full procedure, illustrating removal of the cuneiform tubercles on both sides.

The cranial ends of cuneiform tubercle including their mucosa are removed in a circular pattern before the two incisions are adjoined, thus creating a drop-shaped excision.

Laser surgery dorsal to the corniculate tuberculum is avoided, as scaring in this area could reduce the motility of the posterior part of the aryepiglottic fold. Posterior commissure and the piriform sinus are for this reason protected with wet tissue cloths during the procedure. In case of perioperative oedema of the laryngeal mucosa, corticosteroids are administrated to prevent laryngeal oedema post-operatively. No antibiotic prophylaxis is administered.

### Supraglottoplasty—Minimally Invasive Procedure

The minimally invasive procedure has potential for improving the supraglottic laryngeal obstruction during exercise by “stiffening” the rims of the aryepiglottic fold, thereby preventing inward collapse during high volume ventilation. The method will affect *neither* the anatomical shape/configuration/gross anatomy of the larynx, nor the dimension of the laryngeal inlet at rest. Moreover, the method will not elongate the aryepiglottic fold, and the cuneiform tubercle will not be excised.

The surgeon informs each patient about the objectives of the procedure, as described under the heading “Supraglottoplasty—full procedure” above. The patients are intubated with an armored laser-tube, which is positioned in the posterior midline to protect this area from laser injury. The laryngoscope (Benjamin-Lindholm from Karl Storz) is positioned into the vallecula and the surgical field is visualized through an operation-microscope. The CO_2_-laser (Digital Acublade Lumenis) is attached to the microscope through a micromanipulator, laser energy adjusted to 2–4 W and focused with micro-spot during the procedure. Four punctures are made along the lateral borders of both aryepiglottic fold, thus creating a row of small punctures parallel to the rim of the aryepiglottic fold. The punctions should not be deeper than the incision in the “full procedure” (above); i.e., <5 mm, and care must be taken to avoid thermal damage (e.g., the nervus recurrent posteriorly). It is recommended to protect the posterior commissure and the piriform sinus with wet tissue cloths. No antibiotic prophylaxis is administered. The method is minimally invasive; i.e., if successful, it will in the future be possible to perform this method under local anesthesia.

#### Follow-Up

Patients may be discharged the same day in case of an uneventful procedure. Analgesics may be advised for 3–4 days postoperatively. The patients are advised not to perform hard exercise for the next 10 days. All cases will be scheduled for a follow-up CLE-test with pressure measurement 2–4 months after surgery; however, for participants belonging to the ≪no-surgery control group≫ this will have to take place 2–4 months after surgery would have been performed had they belonged to group E or F (please see Figure 2, Phase 3). Decisions regarding further treatment will rest on the findings from this follow-up, with advice provided individually and in close cooperation with the involved patients. The principles of “shared decision making” will be applied (33).

## Statistical Methods

### Design and Randomization

The main part of the study has a 2 × 2 factorial design with the factors IMT (no/yes) and speech therapy (no/yes). The control arm consists of the patients receiving neither IMT nor speech therapy, only standardized information and breathing advice (IBA). The patients will be randomized in equal numbers to the four arms, using block randomization and the statistical software R. A randomization list will be prepared before the first patient is included. If there is any loss to follow-up, additional patients will be recruited and consecutively assigned to the arm(s) with loss to follow-up. The main analysis will be done on the patients with complete follow-up, but the number of patients lost to follow-up will be reported.

For the surgical sub-study, equal number of patients will be allocated to the three arms, and the randomization will be done using manually shuffled sealed envelopes.

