## Methods

### Subjects and Design

The study will be conducted as a randomized controlled trial, performed at the EILO clinic at Haukeland University Hospital in Bergen, Norway, a nationwide referral center, annually seeing ~200 new patients. All study participants will be recruited from this EILO clinic. The design is outlined in Figure 2. After the diagnostic CLE test, all eligible patients will receive written information about the study. A nurse, not otherwise involved in the study, will provide oral information and be available for questions. Consenting participants will sign a written consent form before inclusion. For patients under the age of 16, their parents must also sign the form. Patients who decline participation will be offered treatment according to present department strategy; i.e., based on a “best practice” approach and according to current department policy for follow-up. We will need 140 patients in phase 1 and 30 patients in phase 3 (see statistics). However, our clinical experience is that ~10% of EILO patients are referred for surgery. The total number of included patients will then be 350.

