### Power Analysis

For practical reasons, we perform the power analysis for a simpler model, where the baseline score is not included. The distribution of CLE scores 2–6 for patients referred to our clinic and meeting the inclusion criteria has been searched in our EILO registry, and found to be 23, 45, 25, 5, and 2%, respectively. We expect that the control group will have a similar distribution, and use this as the basis for the power analysis. We postulate that one of the factors will be effective, with an odds ratio (OR) of 0.3, the other factor will have zero effect (OR = 0) and that there is no interaction. This corresponds to a reduction in mean CLE score of 0.53 for the effective treatment, from 3.18 to 2.65, and is both clinically relevant and in line with effect sizes observed in previous studies (10). The distribution of CLE scores 2–6 will then be 50, 38, 10, 2, and 1%, respectively. (We expect that in practice, some of the patients will have scores below 2, so 2 on this scale should be interpreted as ≤2.) With 35 patients in each arm, computer simulations show that this will give a power of 90% for an overall test of difference between the four arms (even when not using the rule about removing insignificant interactions). An alternative model, where the two treatments have the same effect (OR = 0.3) but there is no additional effect of having both treatments (i.e., a negative interaction) gives a power of 80%. In the actual study, we expect that the baseline score will be a good predictor of the outcome, which will further increase the power.

For the surgical part of the study, the power analysis is similar, with the “no surgery” arm having the same distribution of CLE scores as before (mean score 3.18). However, the effect of the two procedures is postulated as being much larger, OR = 0.05, which corresponds to a mean score in both surgery arms of 2.17. This difference in mean scores of 1.01 is in line with effect sizes from a previous study (11). Including 14 patients in each of the three groups will give a power of ~98% for an overall test (before any adjustment for the baseline scores), and 89% for pairwise comparisons (adjusted for multiple comparisons). The back-up chi-squared test will have a power of 90%. By clinical experience, surgical treatment is provided to ~14% of our EILO population, thus 42 patients entering Phase 3 is a reasonable estimate.

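### Phase 3 assigns surgery or no surgery by hand-shuffled envelopes; a sequence generated in R and held outside the clinic, as is easily done here, would guard better against selective entry

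*Protocol article*

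**What the plan says.** Under Design and Randomization, the four Phase 1 arms are filled "using block randomization and the statistical software R", and "A randomization list will be prepared before the first patient is included". The next paragraph turns to the three surgical arms (full supraglottoplasty, minimally invasive supraglottoplasty, no surgery) and states that "equal number of patients will be allocated to the three arms, and the randomization will be done using manually shuffled sealed envelopes". Nothing more is said about the envelopes.

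The section Phase 3—Surgical Intervention describes candidates as patients with continuing symptoms, a supraglottic score of at least 2 despite non-invasive treatment, and "who are highly motivated for further treatment". It also says that surgery is offered at the hospital independently of the trial. The control group receives no further treatment. The Introduction accepts that raters cannot be blinded after surgery, and the specific aim describes a one-centre study.

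Two sizes are given for Phase 3. Subjects and Design says "We will need 140 patients in phase 1 and 30 patients in phase 3". Power Analysis says "Including 14 patients in each of the three groups will give a power of ~98% for an overall test" and ends with "thus 42 patients entering Phase 3 is a reasonable estimate".

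**The concern.** The plan gives the less checkable allocation method to the phase that most needs protection. Patients reach Phase 3 because they want further treatment. One arm in three offers none, and a patient who declines randomisation can still have the operation. Patients and clinicians therefore have a reason to avoid the no-surgery arm, and a judgement about motivation leaves room to decide who enters and when.

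If an allocation could be learned or changed before entry was final, the patients in the no-surgery arm could differ from those in the two surgical arms before any treatment. Both comparisons with no surgery would then be biased. With 10 or 14 patients per arm, a few such cases would matter. These comparisons are also the evidence for an irreversible procedure.

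**Working it through.** **1. The two methods side by side.**

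| Feature | Phase 1 | Phase 3 |
|---|---|---|
| Source of the sequence | Block randomisation in R | Manual shuffle |
| Fixed in advance | Yes, list before first inclusion | Not stated |
| Can be regenerated from code | Yes, if seed and code are kept | No |
| Option of no added treatment | Reference arm still gets advice and is offered more in Phase 2 | No-surgery arm gets nothing further |
| Preferred treatment available outside the trial | Not the issue | Yes, surgery |

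A full protocol could add numbering, opacity, custody or a log. It could not make a manual shuffle regenerable without changing the method.

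**2. Which Phase 3 size the plan's power figures belong to.** The inputs are the control distribution for scores 2 to 6 (23, 45, 25, 5, 2%) and OR 0.05 in both surgical arms, from Power Analysis, with an assumed two-sided alpha of 0.05. A proportional-odds shift gives means of 3.18 and 2.17, as stated. Simulation gives:
- 14 per arm (3 × 14 = 42): overall power 98.6% (stated about 98%); chi-squared 90.5% (stated 90%).
- 10 per arm (3 × 10 = 30): overall power 92.7%; chi-squared 73.3%.

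The stated power therefore goes with 42, while Subjects and Design gives 30. An equal allocation needs a settled number.

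**3. How predictable one equal deck would be.** Two assumptions are needed, neither of them in the article: all envelopes form one deck with m per arm, and the recruiter knows every earlier allocation. With k envelopes left, the remaining mix is multivariate hypergeometric.

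*Certain as to surgery or no surgery.* With k left, the chance that all are surgery is C(2m,k)/C(3m,k), and the chance that all are no surgery is C(m,k)/C(3m,k). Summing over k ≥ 1 gives the expected numbers of certain allocations, 2m/(m+1) and m/(2m+1).
- m = 14: 28/15 + 14/29 = 1.87 + 0.48 = 2.35 of 42.
- m = 10: 20/11 + 10/21 = 1.82 + 0.48 = 2.29 of 30.

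Only the 0.48 are certain to be no surgery, which is the arm a patient would want to avoid. The last allocation is always certain. With six left in the deck of 42, the chance of certainty is already only 7%.

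*Guessing surgery or no surgery throughout.* Always guessing surgery is right 28 times in 42. The best strategy using the running tally is right 28.8 times, a gain of 0.8. For a deck of 30 it is 20.8 against 20.

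*Guessing the exact arm.* The best strategy is right 18.5 times in 42 (44%, against 33% by chance) and about 65% of the time over the last six. This looks larger, but it includes telling the two operations apart, which has little to do with avoiding no surgery.

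**4. Would a different restriction help?** A maximum tolerated imbalance of 4 between arms was simulated for 42 patients, drawing uniformly among the permitted arms. It lowers exact-arm guessing to 39%. Surgery-versus-no-surgery guesses are still right 28.5 times, and about 4.1 allocations become certain, against 2.35 for the deck. It gains nothing on the contrast that matters. Known blocks of three would be worse, because the last of each block, 14 of 42, would be certain.

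**The case against.** Sealed envelopes are a recognised method and give real concealment for most of the sequence. They can be numbered after shuffling, opened in order, signed and logged. A journal article may leave such details to the full protocol, so their absence here is not a fault. A reader might infer that the method leaves no audit trail, that no envelope is tied to a patient number, or that a redraw could not be detected. The article supports none of these: it is silent, and silence is not evidence that the safeguards are missing.

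A reader might also infer that late allocations are broadly predictable. That rests on a single closed deck and a recruiter who tracks the tally. The article states neither, and if recruitment stops short the certain tail is never reached. Even granting both, the gain is under one patient in 42. This objection stands.

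Two mitigations deserve credit but do not reach the point. The baseline score is in the Phase 3 model, which adjusts for selection on severity as scored, but not on motivation or symptoms. Translaryngeal resistance was added as an objective measure, which limits rater bias in the outcome, but not selective entry.

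What the objection leaves untouched is the stated choice of method. The article itself specifies a hand shuffle, in a setting with a plain incentive to avoid one arm, although the team already generates a list in R for Phase 1.

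**Conclusion.** The point holds as a design weakness that is worth correcting. No stated figure is wrong because of it, and nothing shows that allocation would in fact be subverted. It rests on what the article states: a manual shuffle, an open single-centre comparison, partly discretionary entry, and surgery available elsewhere. The sequence cannot be regenerated and checked, and physical envelopes protect concealment less well than a list held away from recruitment. Any resulting selection bias cannot be sized from the document.

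Predictability is a minor, conditional addition: about 2.3 certain allocations of 42 as to surgery versus no surgery, and a total guessing gain of 0.8 patient. It should not be used as the main argument. The conflict between 30 and 42 patients is a separate inconsistency that leaves the number of allocations to prepare undefined.

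**What to change.** Replace the envelope sentence in Design and Randomization. Suggested content: the Phase 3 sequence is generated in R before the first Phase 3 patient, with seed and code kept. Someone outside the clinic, for example the trial statistician, holds it. Each allocation is released singly, after consent and the baseline tests (including the exercise laryngoscopy with resistance measurement) are logged under the patient's number.

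Equal allocation can stay, provided that any block structure is not disclosed to recruiters. A maximum-tolerated-imbalance rule is not needed. Before the list is generated, reconcile the Phase 3 size between Subjects and Design (30) and Power Analysis (42).

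The cost is one changed sentence, a short script, and a contact with the list holder for each Phase 3 patient. The change improves checkability and concealment. It does not by itself make an equal sequence harder to guess near its end.

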### Statistical Model

The primary outcome is CLE score obtained close to peak exercise, measured on an ordinal 0–6 scale. For the main analysis, a proportional odds (cumulative logit) model will be fitted to the data. The explanatory variables will be the two treatment factors, their interaction and the baseline CLE score (as a continuous/linear variable). If the interaction is clearly insignificant, *P* ≥ 0.20, it will be removed from the model, and the results will be reported for the simplified model. The results will be presented as odds ratios (with the control arm as the reference group) with confidence intervals (CIs). Mean scores for the four arms will also be reported, with CIs calculated using the percentile bootstrap. If the baseline score is statistically significant (*P* ≤ 0.05), estimated model-based probabilities of obtaining the various CLE scores based on baseline CLE score and treatment arm will be reported.

A similar proportional odds model will be fitted for the surgical part of the study, the only difference being three instead of four treatment arms. With the relative small number of patients, there is a risk of non-convergence of the ordinal model (mainly if all patients in an arm end up with the same score). In this case, we will instead use a chi-squared omnibus test, followed by pairwise chi-squared tests. The *P*-values from these pairwise tests will be adjusted for multiple comparisons using Fisher's procedure (34).

There is uncertainty in how the proposed ordinal models will fit the data. We may need to do some adjustments to the model to improve model fit (e.g., include the baseline scores as a quadratic instead of a linear term), or possibly use other statistical models. If no statistical model can be found that adequately fits the data, we will simply report the score distribution in the four/three arms, along with mean scores and corresponding confidence intervals.

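### Phase 3: the back-up for a non-converging ordinal model discards score order, baseline score and the odds ratio, chiefly when surgery has worked well; an order-preserving back-up would cost only wording

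*Protocol article*

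**What the plan says.** Under Statistical Model, the Phase 1 analysis is a proportional odds model whose explanatory variables are the two treatment factors, "their interaction and the baseline CLE score (as a continuous/linear variable"). Results are to be given as odds ratios with confidence intervals. For Phase 3: "A similar proportional odds model will be fitted for the surgical part of the study, the only difference being three instead of four treatment arms". The baseline score and the odds ratios therefore carry over.

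The protocol then warns that "there is a risk of non-convergence of the ordinal model (mainly if all patients in an arm end up with the same score"), and provides: "In this case, we will instead use a chi-squared omnibus test, followed by pairwise chi-squared tests". The pairwise P-values are to be "adjusted for multiple comparisons using Fisher's procedure (34").

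Power Analysis postulates an odds ratio of 0.05 for both operations with 14 patients per arm. It gives about 98% for the overall test and adds: "The back-up chi-squared test will have a power of 90" per cent.

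On arm means, the sentence is "Mean scores for the four arms will also be reported, with CIs calculated using the percentile bootstrap". For three arms, means with intervals are mentioned only for the case where no model fits adequately, and no interval method is named there.

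**The concern.** The outcome is ordinal and bounded below. If surgery succeeds, an arm can end with every patient in the lowest observed category. The maximum likelihood odds ratio for that arm is then infinite and the fit does not converge. An arm constant at a middle score does not have this effect. The rule therefore switches method according to the outcome, mostly in the direction of benefit.

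The method switched to is a poor match. Pearson's chi-squared treats the scores as unordered labels, cannot use the baseline score that the protocol expects to be a good predictor, and yields no odds ratio. It also relies on a large-sample approximation with 14 patients per row. At stake is how a clear result for an irreversible operation would be tested and reported.

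**Working it through.** **Inputs (Power Analysis).** Control distribution over scores 2 to 6: 23, 45, 25, 5, 2%, where 2 stands for 2 or lower. OR 0.05 in both surgery arms; 14 per arm. Alpha 0.05 is an assumption, as the protocol states none for these calculations. Subjects and Design gives 30 Phase 3 patients rather than 42; that is a separate matter, and 14 per arm is used here.

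**Surgery distribution.** Divide the control odds of scoring 2 or lower by 0.05: 0.23/0.77 = 0.2987; 0.2987/0.05 = 5.974; 5.974/6.974 = 0.857. Repeating this at each cut-point gives 0.857, 0.120, 0.019, 0.003, 0.001, with mean 2.17. The difference from 3.18 is 1.01. Both match the protocol.

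**The protocol's own power figures.** In 3,000 simulated trials without the baseline score, the proportional odds likelihood-ratio test gave 98.7% (stated: about 98%) and the unordered Pearson chi-squared test 90.5% (stated: 90%). A Kruskal-Wallis test gave 98.5%, so the stated 90% does refer to an unordered test. The stated 89% for pairwise comparisons was not reproduced, but nothing below depends on it.

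**How often the trigger occurs, with scores of 2 or lower pooled.**
- One given surgery arm: 0.8566^14 = 0.1145.
- At least one of two: 1 − (1 − 0.1145)^2 = 0.216.
- By effect size: 0.01% at OR 0.3, 3.5% at OR 0.1, 21.6% at OR 0.05, 64% at OR 0.02.

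**The same if some surgery patients score 1.** Let a fraction f of the surgery patients at 2 or lower score 1 (an assumption; the protocol gives no split). Separation then needs one arm entirely at 2 and no 1 in the other surgery arm. Write A = [(1 − f) × 0.8566]^14 and B = (1 − f × 0.8566)^14. The probability is 2AB − A².
- f = 5%: A = 0.0559, B = 0.542; 2 × 0.0559 × 0.542 − 0.0559² = 0.057, about 6%.
- f = 20%: A = 0.00504, B = 0.0720; the result is 0.0007, about 0.1%.

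**Behaviour of the fit.** With an arm all in the lowest category, the estimate diverged (log OR about −17, standard error about 659). With an arm constant at a middle score it stayed finite (−0.72, standard error 0.86). In the separated case the likelihood-ratio statistic is still computable.

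**Sparseness.** Mean expected count per arm in the lowest column: (14 × 0.23 + 28 × 0.8566)/3 = 9.1. The other columns give 3.2, 1.4, 0.3 and 0.1. With empty columns dropped, about 72% of expected counts are below 5. The chi-squared test is conservative here: its size is 3.3% under the control distribution and 2.4% under the surgery distribution.

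**Cost of the rule as written** (chi-squared only when triggered, a rank test standing in for the ordinal model otherwise, scores pooled):

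| | Chi-squared back-up | Rank test |
|---|---|---|
| Overall test, all trials | about 98% | about 98% |
| Overall test, triggered trials | about 99% | above 99% |
| Both surgery arms beat control, triggered trials | about 87% | about 96% |
| Both surgery arms beat control, all trials | about 92% | about 94% |

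Repeated runs put the triggered-trial figures at 85 to 88% against 95 to 97%. As a check, 0.21 × (96 − 87) is about 2 points, which is the difference in the last row.

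**The case against.** The protocol foresees the problem, names a substitute and openly states its lower power, and that figure reproduces. The substitute is conservative, so it adds no false-positive risk. All of this stands: the choice is improvable and is neither an error nor a contradiction.

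Four stronger readings are tempting and are not supported.

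- **The sub-study loses 8 points of power (98% to 90%).** This would apply chi-squared to every trial. The protocol uses it only after non-convergence, when the effect is so large that the overall test still rejects in about 99%.
- **The best surgical result would be missed.** The constant arm itself beats control in about 99% of triggered trials even with chi-squared. The loss in the both-arms figure falls almost entirely on the other surgery arm.
- **One trial in five will trigger the rule.** That needs every score of 2 or lower to be identical. The analysis scale is 0 to 6 and the protocol expects some scores below 2, so about 21% is an upper figure under its assumed effect.
- **The arm mean will be reported with a zero-width interval.** The percentile bootstrap is named only for the four Phase 1 arms. Its use in Phase 3 is an inference from the statement that only the number of arms differs.

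Nor would the report be empty. Arm means and score distributions can still be given, although the protocol ties them to poor model fit rather than to this case. What is lost is the odds ratio and its interval.

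**Conclusion.** The point holds in a limited form. The protocol fixes an unordered, baseline-unadjusted back-up for an ordinal outcome, and its main trigger is a floor effect that grows with surgical benefit. The consequences are loss of the promised odds ratio with interval, loss of baseline adjustment, reliance on a sparse table, and about 2 points of power for showing that both operations beat control. Overall power is essentially unchanged.

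These sizes assume 14 per arm, OR 0.05 in both surgery arms, alpha 0.05, no baseline term and pooled scores of 2 or lower. With scores below 2 spread out, the rule would rarely be used and the cost shrinks accordingly. This is an improvement to consider, not a condition for the trial's validity.

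**What to change.** Replace the chi-squared back-up with a method that keeps the score order, in one of two ways:

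1. The proportional odds likelihood-ratio test, which remains usable under separation and keeps the baseline score. In the simulated triggered trials, fitted without baseline, it rejected in 100%.
2. An exact permutation Kruskal-Wallis test, followed by exact Wilcoxon tests under the same Fisher procedure. This cannot fail to converge, but it does not use the baseline score.

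In either case, report odds ratios from a penalised proportional odds fit with profile-likelihood intervals, and restate the 90% back-up power for the new test. On the protocol's assumptions a rank test has about 98%.

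If the percentile bootstrap is also meant for Phase 3 means, say so and name an interval that does not collapse when an arm is constant. With 14 identical scores of 2 it returns [2.00, 2.00]. Yet 0 of 14 patients above 2 is compatible with a true rate of up to 1 − 0.025^(1/14) = 23%.

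The cost is a few sentences and standard software, settled before outcome data are seen. No extra patients are needed.
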